**Methods/design:**

This study is a single-blind, randomized controlled trial. A random number table will be generated by an independent person. Each number will be placed in a sealed opaque envelop to blind assignment. All outcome assessors will be blinded to group assignment.

COPD patients between 40 and 80 years of age, with stable medical treatment and no regular participation in regular exercise in the last 6 months will be included. All participants will be recruited from the Respiratory Medicine Department of Yue-Yang Integrative Medicine Hospital Affiliated to Shanghai University of Traditional Chinese Medicine.

All participants will continue to follow their medical treatment. They will be randomly assigned to one of four groups in a 1:1:1:1 ratio: (1) usual care (control group, CG), (2) pulmonary exercise group (PG), (3) resistance exercise group (RG), or (4) combined pulmonary exercise and resistance exercise group (PRG). CG participants will receive medical treatment only. PG participants will perform 60 min of exercise twice a day 7 days a week for 3 months, with 1 day’s exercise per week at hospital under guidance and supervision. RG participants will perform 60 min of resistance exercise once a day, three times a week for 3 months, with 1 day’s exercise per week at hospital under guidance and supervision. PRG participants will perform 60 min of prescribed pulmonary exercise combined with resistance exercise for 3 months.

The outcomes include the isokinetic strength of peripheral skeletal muscle, surface electromyography, 6-min walking distance, 30-s arm curl test, pulmonary function, respiratory muscle strength, dyspnea, body composition, physical activity, quality of life, and Chronic Disease Self-Efficacy Scale.

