Hence, in this study, 3 months of (1) usual care, (2) prescribed pulmonary exercise, (3) exercising with resistance bands, and (4) prescribed pulmonary exercise combined with exercising with elastic bands will be applied as interventions to COPD patients to evaluate the overall effect of prescribed pulmonary exercise on lung function, exercise capacity, skeletal muscle function, quality of life, and psychological function in patients with COPD. The aim of the study is to further clarify the role of prescribed pulmonary exercise in COPD rehabilitation, since it is a simple, fun, easy to learn, operational, and effective intervention for COPD patients. We hypothesize that prescribed pulmonary exercise can significantly improve pulmonary function, exercise capacity, skeletal muscle function, quality of life, and psychological function, and that combined exercise induces additional benefits in COPD patients compared with single exercise methods.

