### Sample size

The sample size was based on detecting a minimum difference of 54 m in the 6MWT [11] between the control group (CG) and the pulmonary exercise group (PG) and used a baseline standard deviation of 57 m [11]. With a power of 80% and an alpha of 5% (two-sided), the minimum sample size per group is 18 to give a total of 72 participants. Assuming a drop-out rate of 20%, the minimum sample size in total is 88 (22 participants in each group). The participants will be recruited to achieve a balanced number of patients with different levels of severity of COPD.

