### Outcome measurement

All participants will undergo assessments within 1 week of being enrolled at baseline and at the end of 3 months. The primary outcomes are the pulmonary function test, 30-s arm curl test, and 6MWT. Secondary outcome measures include the Modified Medical Research Council Dyspnea Scale (mMRC), dual-energy X-ray absorptiometry (DXA), respiratory muscle strength test, peripheral skeletal muscle strength, sEMG, and questionnaires.

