### Statistical analysis

SPSS version 23.0 will be used for data management and statistical analysis. A Kolmogorov–Smirnov test will be used to test for normality, and the normality data will be expressed as mean ± standard deviation, while skewed data will be expressed as median and interquartile range. An intention-to-treat analysis will be used for the allocation, irrespective of whether the participant completes the intervention. Missing outcome data will be handled using a mixed-model method. Then a per-protocol analysis will be conducted, which will include only subjects who completed all outcome measures and followed the intervention protocol. Comparisons of baseline differences between groups will be performed using one-way analysis of variance (ANOVA) or a non-parametric test. Training-related effects will be assessed using 2 × 2 ANOVA (group × time). Differences between variables over time (time effect, from baseline to 3 months) in each group will be evaluated using a paired *t*-test or a non-parametric test. For categorical variables, a chi-squared test will be employed to detect differences. A two-tailed *P* value of <0.05 will be considered to be significant. In addition, differing intervention effects on pulmonary function have been found in previous studies [4, 32, 33], and disease severity may be an important contributor. Therefore, a pre-specified subgroup analysis will be performed to investigate the differences in effectiveness according to disease severity.

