There are several highlights to this study. First, the prescribed pulmonary exercise is a rearrangement of traditional Chinese exercise and targeted to COPD patients. The effects of this prescribed pulmonary exercise on lung function, respiratory muscle strength, exercise capacity, skeletal muscle function, quality of life, and physical activity on stable COPD patients will be evaluated. Second, the role of prescribed pulmonary exercise in improving skeletal muscle function and exercise capacity will be determined by comparing the effects of pulmonary exercise and an elastic band program. Third, the effect of pulmonary exercise combined with exercising with elastic bands in stable COPD patients will be determined, and the effects compared with a single program to determine whether combined exercise can achieve additional beneficial effects. Fourth, the study will apply comprehensive measurements to evaluate skeletal muscle function in patients with COPD, including isokinetic muscle strength testing, surface myoelectricity, 6MWT, and the 30-s arm curl test. Fifth, a sub-analysis will be performed to investigate if the treatment effects differ in patients with different disease severity to enable the optimization of treatment effects for all patients suffering from the troublesome disease. Finally, the study is in strict accordance with CONSORT guidelines, so that the effects of the prescribed pulmonary exercise can be clearly determined.

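### The test of training effects is a 2 × 2 (group × time) ANOVA, but the trial has four arms at two visits; the model holds only two arms and the protocol does not say which

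*Protocol article*

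**What the plan says.** All from the protocol article.

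- **Statistical analysis:** "Training-related effects will be assessed using 2 × 2 ANOVA (group × time"). The same section gives one-way ANOVA for baseline differences, paired tests within each group, a chi-squared test for categorical variables and a mixed-model method for missing outcome data.
- **Abstract, Methods/design:** "They will be randomly assigned to one of four groups in a 1:1:1:1 ratio". The arms are control (CG), pulmonary exercise (PG), resistance exercise (RG) and both combined (PRG).
- **Outcome measurement:** "All participants will undergo assessments within 1 week of being enrolled at baseline and at the end of 3 months". That gives two time levels.
- **Sample size:** "The sample size was based on detecting a minimum difference of 54 m in the 6MWT" "between the control group (CG) and the pulmonary exercise group (PG"). The calculation "used a baseline standard deviation of 57 m".
- **Background, closing paragraph:** the second hypothesis is that "combined exercise induces additional benefits in COPD patients compared with single exercise methods".
- **Discussion, list of highlights:** for the combined programme, "the effects compared with a single program to determine whether combined exercise can achieve additional beneficial effects".

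**The concern.** The 2 × 2 ANOVA is the only between-arm test of change that the article names for the continuous outcomes, and these include all three primary outcomes. Its stated dimensions do not match the design. A two-level group factor leaves two arms out, and the Statistical analysis section does not identify the pair. The Sample size section singles out PG and CG but does not link that pair to the ANOVA, and the pair cannot serve the combined-versus-single hypothesis.

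This is not a detail left to a fuller document. The protocol fixes a specific dimension, and that dimension conflicts with its own design. The possible corrections also test different things: a set of pairwise models tests named differences, whereas a 4 × 2 interaction tests whether any of the four arms differs in change.

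**Working it through.** **1. Dimensions.** With g groups and t times, the interaction has (g − 1)(t − 1) df. With N participants, its error term has (N − g)(t − 1) df.

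| Model | N | Interaction df | Error df |
|---|---|---|---|
| Four arms × two times | 72 | 3 × 1 = 3 | 72 − 4 = 68 |
| Two arms × two times | 36 | 1 × 1 = 1 | 36 − 2 = 34 |

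Four arms form 4 × 3 / 2 = 6 possible pairs, so six different 2 × 2 models fit the words.

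**2. The protocol's own sample size.** Inputs from the Sample size section: difference 54 m, SD 57 m, two-sided 5%, power 80%.

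n = 2 × [(1.960 + 0.842) × 57/54]² = 17.5, rounded up to 18 per group; 4 × 18 = 72. The stated figures reproduce (normal approximation; power 81.1% at n = 18).

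**3. PG versus CG: pairwise model or four-arm model.** With two visits, the interaction contrast is the between-arm difference in change. Taking 57 m as the SD of change, the standard error is 57 × √(2/18) = 19.0 m and the noncentrality is 54/19.0 = 2.84.

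| Model | Error df | Critical t | Power | 95% CI half-width |
|---|---|---|---|---|
| Pairwise 2 × 2 | 34 | 2.032 | 78.8% | 2.032 × 19.0 = 38.6 m |
| Four-arm model | 68 | 1.995 | 80.0% | 1.995 × 19.0 = 37.9 m |

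The cost of going pairwise is 1.2 points of power and 0.7 m of half-width.

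**4. The 3-df interaction read alone.** Noncentral F(3, 68), with λ = 18 × Σ(mean − grand mean)² / 57². Mean changes are relative to CG, in the order CG, PG, RG, PRG. The protocol gives only the 54 m for PG; the other means are assumptions chosen to show the range.

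| Assumed means (m) | λ | Power |
|---|---|---|
| 0, 54, 27, 27 | 8.08 | 63% |
| 0, 54, 0, 0 | 12.12 | 82% |
| 0, 54, 54, 54 | 12.12 | 82% |
| 0, 54, 27, 68 | 15.06 | 90% |
| 0, 54, 54, 81 | 19.18 | 96% |
| 0, 54, 27, 81 | 20.19 | 97% |

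The last three rows follow the trial's hypothesis that the combined programme does better than either single one. The PG−CG difference is 54 m in every row, yet power runs from 63% to 97%. The omnibus result therefore says little about that contrast in particular.

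**5. Sensitivity to the SD.** The protocol calls 57 m a baseline SD. With equal SDs at both visits and within-person correlation r, the SD of change is 57 × √(2(1 − r)), which equals 57 m only at r = 0.5. The documents give no r.

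| Assumed r | SD of change | Pairwise power | Four-arm power |
|---|---|---|---|
| 0.3 | 67.4 m | 65% | 66% |
| 0.5 | 57.0 m | 78.8% | 80.0% |
| 0.7 | 44.2 m | 95% | 95% |

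The level moves a good deal; the gap between the two models stays near 1 point.

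**6. Does any other sentence repair it?** The arms do form a factorial (pulmonary yes/no by resistance yes/no), but the factors named are group and time, and adding time to that factorial would make it 2 × 2 × 2. The mixed-model sentence concerns missing data and gives no group structure. The one-way ANOVA is for baseline, the paired tests are within group, and the chi-squared test is for categorical variables. None supplies a four-arm test of change.

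**The case against.** The best defence is that the label is a slip and the intended analysis is easy to guess. Pairwise 2 × 2 ANOVAs fit the words, can test every comparison the protocol says it wants, and lose about 1 point of power. A common error term also assumes equal variance across all four arms, so pairwise models are a defensible choice. All of that stands. A reader might infer that the stated model cannot test the trial's comparisons; run pairwise, it can. The protocol simply does not say that it is to be run that way, or on which pairs.

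Three other strong readings are tempting and not supported:

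- **That the three exercise arms might be pooled against control.** No section suggests it. The Background and Discussion describe arm-by-arm comparisons, and the Sample size section names CG and PG.
- **That the omnibus interaction is underpowered.** The 63% case puts PRG midway between CG and PG, against the trial's own hypothesis. Under patterns consistent with that hypothesis, power is 90% to 97%.
- **That the deciding comparison would be chosen after the data are in.** A statistical analysis plan may exist and may name the contrasts; the documents at hand do not show otherwise.

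The defence does not remove the conflict itself: the article states a dimension that its own design contradicts, and a separate plan would have to depart from it or name the pairs.

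**Conclusion.** The sentence is wrong as written. Four arms and two assessments make a 4 × 2 layout (3 interaction df, not 1), and the stated 2 × 2 model covers two unnamed arms. Confidence in the mismatch is high, because it rests only on counting arms and visits.

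The consequence is one of definition more than of power. Run pairwise, the cost for PG−CG is 78.8% against 80.0%. Changed to 4 × 2 with only the interaction read, the test does not by itself answer PG versus CG, PRG versus PG or PRG versus RG, and its power falls on either side of 80% according to the true means. These figures assume 18 completers per arm, a true 54 m difference and 57 m as the SD of change. For correlations of 0.3 to 0.7, pairwise power is about 65% to 95%. The correction should be made, but the mismatch does not invalidate the design.

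**What to change.** Replace the 2 × 2 sentence with wording to this effect: *Training-related effects on continuous outcomes will be analysed in one model with a four-level group factor and two times (a 4 × 2 group × time ANOVA, or the equivalent four-arm mixed model). The tests of interest are the between-arm differences in change from baseline to 3 months for PG−CG, PRG−PG and PRG−RG, estimated from that model. The 3-df group × time interaction is supportive.*

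The contrasts should be worded as differences in change. In a group × time ANOVA, that is the quantity that uses the common interaction error term; a between-arm difference at 3 months alone is a different quantity with a different error term. If pairwise 2 × 2 models are what is meant, the alternative is to say so and list the pairs.

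The cost is one sentence of analysis text, with no new participants, visits or measurements. The article reports the trial as still recruiting, so the change can be recorded as an amendment.

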### Intervention

All participants will continue with their prescribed medication. They will attend the same weekly educational sessions including on quitting smoking, self-management, and nutrition. In addition, participants in the exercise groups will attend 3 exercise sessions over 2 weeks to become familiar with the intervention programs. During this study time, the participants will be given oral and visual instructions on how to perform the prescribed pulmonary exercises or the exercises with elastic bands and will be given instructions on how to perform the exercises at a Borg CR10 intensity level of between 4 and 6 [23]. In addition, all participants in the exercise groups will receive a teaching video and exercise record book. After each exercise session, participants will be required to record what they have done, including but not limited to time, duration, intensity, and site (home or other).

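### Paired tests within each arm share the P<0.05 threshold and are not marked descriptive, so a significant change in the pulmonary exercise arm could be mistaken for a treatment effect (minor)

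*Protocol article*

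**What the plan says.** All of the analysis text is in the Statistical analysis section of the protocol article.

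- Treatment analysis: "Training-related effects will be assessed using 2 × 2 ANOVA (group × time").
- The next sentence adds a test inside every arm: "Differences between variables over time (time effect, from baseline to 3 months) in each group will be evaluated using a paired" (meaning a t-test, or its non-parametric counterpart).
- One threshold, two-tailed, is given for everything: a P "value of <0.05 will be considered to be significant".
- A non-parametric alternative is named for the baseline comparison and for the within-arm tests. None is named for the group × time analysis.

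Three other places bear on how the results will be read.

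- The hypothesis at the end of the Background: "We hypothesize that prescribed pulmonary exercise can significantly improve pulmonary function, exercise capacity, skeletal muscle function" and further outcomes. A comparator (single exercise methods) appears only in the later clause on combined exercise.
- The Intervention section, on all participants: "They will attend the same weekly educational sessions including on quitting smoking, self-management, and nutrition".
- The Sample size section plans on a between-arm difference: "detecting a minimum difference of 54 m in the 6MWT [11] between the control group (CG) and the pulmonary exercise group (PG").

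**The concern.** A paired test inside one arm asks whether those patients changed. It does not ask whether the allocated treatment changed them, and it makes no use of the randomised comparison. Anything that moves all arms together counts towards significance. Here that could include the shared weekly education, the attention of being in an unblinded trial, and the repetition of effort-dependent tests.

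Two features make a misreading easier in this protocol. The hypothesis for pulmonary exercise alone is worded as significant improvement without a comparator, so a small within-arm P value would literally appear to satisfy it. For skewed outcomes, the within-arm test is also the only test of change for which the section states a non-parametric method.

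What is at stake is a report that presents significance in PG and non-significance in CG as evidence of benefit. A difference between two P values is not a test of the difference between two arms.

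**Working it through.** **Inputs from the article.** SD 57 m ("used a baseline standard deviation of 57 m [11"]), difference 54 m, two-sided 5%, power 80%, 18 per arm analysed, 22 per arm recruited.

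**Assumptions, not in the article.** The correlation ρ between baseline and 3-month 6MWT, the gain shared by all arms, equal SDs at both visits, and independent arms.

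**1. The plan's own figure.** n per arm = 2 × (1.960 + 0.842)² × 57² / 54² = 17.49, rounded up to 18. This reproduces the stated 18 per group, and it is a between-arm calculation.

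**2. Chance that one paired test is significant when treatment does nothing.** SD of change = 57 × √(2(1 − ρ)). At ρ = 0.7 this is 57 × √0.6 = 44.2 m. With a shared gain of 20 m and n = 18, the non-centrality is 20 / (44.2/√18) = 1.92. The non-central t distribution on 17 df then gives p = 0.442 for a significant improvement in any one arm.

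**3. Chance that PG improves significantly and CG is not significant.** With independent arms and equal true change, this is about p(1 − p). At the values above, 0.442 × 0.558 = 0.247.

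**4. Range (n = 18).**

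| Shared gain | ρ = 0.6 | ρ = 0.7 | ρ = 0.8 |
|---|---|---|---|
| 0 m | 0.024 | 0.024 | 0.024 |
| 5 m | 0.055 | 0.061 | 0.073 |
| 10 m | 0.105 | 0.125 | 0.159 |
| 15 m | 0.170 | 0.199 | 0.237 |
| 20 m | 0.227 | 0.247 | 0.240 |
| 25 m | 0.250 | 0.236 | 0.165 |
| 30 m | 0.227 | 0.174 | 0.079 |

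The zero-gain row is 0.025 × 0.95 = 0.024. For gains of 10–25 m the range is 0.105 to 0.250. With 22 per arm it is 0.11 to 0.25.

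**5. Upper bound.** p(1 − p) is largest at p = 0.5, where it equals 0.25. This bound does not depend on the assumed gain or correlation. If exactly one of the two arms being significant counted, in either direction, the bound is 2 × 0.25 = 0.50.

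**6. Comparator.** A valid two-sided 5% test favours PG falsely 2.5% of the time. In a simulation with n = 18, ρ = 0.8 and a shared gain of 17.5 m (100,000 runs), the comparison of change between arms, which is the group × time test at two visits, rejected in 5.0% of runs. The pattern PG significant and CG not occurred in 25.0%.

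**7. Gain from baseline adjustment.** Per arm, the change score has variance 2σ²(1 − ρ) and the baseline-adjusted outcome has σ²(1 − ρ²). The ratio is (1 + ρ)/2, which is 0.75 at ρ = 0.5 and 0.90 at ρ = 0.8. Adjustment therefore has 25% to 10% less variance than the group × time comparison. This ignores the small cost of estimating the slope.

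**The case against.** The strongest reply is that the section already separates the two roles. Training-related effects go to group × time, and the paired tests are labelled a time effect. A reader might infer that the paired tests are planned as the effect analysis. The text does not support that, and nowhere does the article say that a treatment effect will be concluded from differing P values. The Design section frames the trial as a comparison of four arms, and the sample size rests on CG against PG. All of this stands, and it is why the point is minor.

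A reader might also infer an error rate ten times nominal. For PG significant and CG not, the peak of 25% is five times the protocol's two-sided 5%. It is ten times only against the single 2.5% tail that favours PG. Tenfold against 5% requires counting either direction (50%).

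The size also depends on the assumed shared gain. With none there is no inflation, and at 30 m the rate is falling again. A learning effect on the 6MWT is limited because the test is done twice at each assessment and the longer distance is used. Patients are not selected on 6MWT and must be clinically stable, so regression to the mean has little support for that outcome.

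Finally, reporting change within arms is common, and a separate analysis plan might call it descriptive. The article as written, however, states these as tests under the common 5% threshold with no such label, beside a hypothesis for PG that has no comparator. That part of the concern survives.

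**Conclusion.** The point holds as a minor one. Within-arm paired tests are planned at the common P<0.05 without being marked descriptive. They could appear to confirm the PG hypothesis even if every arm improved equally. The protocol does not commit to that reading, and its group × time analysis holds its error at 5% when it is used.

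If the pattern PG significant and CG not were nevertheless taken as a treatment effect, the false-positive rate would be about 2.4% with no shared change and 11–25% for shared gains of 10–25 m with correlations of 0.6–0.8. It could not exceed 25%, against 2.5% in that direction for a valid between-arm test. The gains and correlations are assumptions; the 25% ceiling is not, given independent arms with equal true change and equal chance of significance.

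**What to change.** In the Statistical analysis section, drop the within-arm P values or label them descriptive, and report mean change with a 95% CI for each arm. State that every claim of effect, including PG against CG, rests on the between-arm difference at 3 months adjusted for baseline. Word the PG hypothesis as a comparison with usual care.

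The change uses data already planned for collection and needs no more patients or visits. Under the equal-variance assumption above, baseline adjustment also cuts the variance by 10–25% relative to the change-score comparison. The cost is the loss of the within-arm P values as evidence.
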